### Sample size

3.3

The simple size was calculated considering the following parameters: an expected difference in the study outcomes (overweight, obesity, and alteration of the lipid profile) of 20% between the intervention group and the control group; a power of 90%, an alfa of 5%, an intervention group/control group ratio of 1:1, and a 20% adjustment for losses to follow-up, resulting in a sample of 270 participants (n = 135 intervention and n = 135 control group). The OpenEpi software was used for the calculation. Since this is a pilot study and considering the feasibility, the research team decided on a sample size of 150 participants (n = 75 intervention group and n = 75 control group).

### Randomization and blinding

3.4

The randomization process will take place in 2 stages. An engineer from the data central will conduct the randomization of the list of the 217 potentially eligible participants by means of a computer program with random numbers and it will select 150 individuals to participate in the study. Subsequently, a nurse will make phone calls to schedule appointments and formalize the participation in the study, the signature of the informed consent, and the taking of baseline measures. Once these stages are concluded, the assignment of treatment in real time will be made with the support of a computer program. The procedure will take place by means of a single assignment sequence that determines the assignment code for each participant's treatment. This process allows all participants in the study to be assigned to any of the treatment groups. The intervention group will receive 1000 IU of VD while the control group will receive 200 IU of VD.

Supplements will be packaged in individual packages with the total number of doses per participant (105 doses). The coding of the packages will be in charge of the laboratory in charge of providing the supplements, which in turn will send to the designated person at the data center by institutional e-mail, a document with the list of codes and the dose of the supplement.

The 1000 IU and 200 IU doses of VD will be provided in white containers and will be identical in terms of physical and organoleptic characteristics, to ensure that both participants and investigators are blinded to the treatment. To maximize adherence to the intervention, participants will be required to cross out daily supplementation on a calendar with the study period, which they will be required to return at the end of the study.

The results of the assignment will only be known by the systems engineer at the data center. In other words, this information “will not be visible” to the coordinating nurse, laboratory personnel in charge of processing biological samples, pediatrician, principal investigator of the study, or the epidemiologist in charge of quality control and data analysis. This will ensure the masking of the people in charge of measuring the outcomes, administering the intervention and analyzing the study data.

### Recruitment

3.5

For recruitment, a study nurse in charge of enrollment will contact by phone the 217 successful participants of the third re-contact, explain the objective of the study and inquire about the interest to participate; if there is a positive response, inclusion and exclusion criteria will be verified. A list of eligible participants will be generated from the above process and sent to the person in charge of the randomization process.

After the randomization process, the study nurse will receive from the data center the list of the 150 participants selected, who will be invited to participate in the clinical trial. The nurse will call them on the pone for a face-to-face appointment where the details of the study will be informed, doubts will be clarified, and the informed consent form will be signed; a copy of the form will be given to the participant.

During that appointment, the collection of demographic and clinical data will take place, as well as a blood simple for further measurement of VD, lipid profile and glycaemia; the anthropometric nutritional, dietary and physical activity assessment will also be carried out. Once the baseline measurements are taken, the assignment to the intervention will be made in real time through software designed for the study.

Finally, the supplementation intervention will be explained in detail and the package corresponding to the participant's code will be delivered according to the process of assignment to the group (intervention/control), it will be clarified that the supplementation will last 15 weeks and then the second meeting will be scheduled to carry out again the measures taken at the beginning of the study. At the end, a third meeting will be scheduled for the delivery of results and recommendations.

### Interventions

3.6

The intervention group will receive 1000 IU of VD and the control group 200 IU of VD daily for 15 weeks. All participants will be given 105 doses of VD. The supplementation will be provided by the laboratory *Farma de Colombia* and is commercially named as Farma D. Its commercial presentation is soft gelatin capsules.

The 75 participants assigned to the intervention group will take one (1) 1000 IU VD capsule daily for 15 weeks. The daily dose selected is based on the amount required for replenishment over a period of approximately 3 months, and is well below the intake levels associated with toxicity.^[16]^ On the other hand, the 75 participants in the control group will take 1 capsule of VD of 200 IU daily for 15 weeks, since the benefits of VD for the health of people have been demonstrated, this being the minimum recommended dose for children. The above, considering that it is unethical for the control group not to receive any type of supplementation.

The participants in both the intervention and the control group must record in a calendar the time of the daily intake of the supplement during the 15 weeks.

### Follow-up

3.7

Follow-up will be done 15 weeks after the start of the study (after the end of the intervention).

In addition, all participants will be followed up with a telephone call at weeks 1, 2, 5, 7, and 12. These calls will inquire about any “potential” adverse effects related to the intervention and assess adherence to DV sampling by means of a self-reporting instrument (Table 1).

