Consequently, research has recently begun on the efficacy of VD supplementation in children. Thus, Rajakumar et al, found that the correction of VD levels in overweight and obese children, by administering vitamin D3 with 1000 or 2000 IU/day versus 600 IU/day, had no statistically significant effect on measures of arterial endothelial function or stiffness, systemic inflammation or lipid profile, however, they were able to evidence a reduction in blood pressure, glucose levels and improvement in insulin sensitivity, suggesting that optimization of the VD status of children can improve their cardiovascular health.^[14]^

Likewise, Marwaha et al, showed that VD supplementation with the three daily doses of vitamin D3 (600, 1000, and 2000 IU) lead to a significant increase on the serum levels of 25 (OH) D in school children with VDD and the secondary hyperparathyroidism decreased from 31.7% to 8.4% after supplementation.^[15]^

A significant aspect to consider in the vitamin D supplementation interventions is that they are low cost, easy to implement and very safe; consequently, if a positive effect is achieved, a problem of great impact and increasing prevalence, such as the metabolic syndrome and cardiovascular risk, would be intervened.

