### Safety considerations

3.8

The recommendation of vitamin D in the diet for the Colombian population (males-females) is 600 IU/day, a value equivalent to a nutritional density of 40 IU/1000 Kcal. In adolescence, plasma levels decrease and needs increase; however, the recommendation is the same as for adults.^[17]^

Normally there is no toxicity by VD since it is a fat-soluble vitamin and the organism excretes it regularly. Thus, the causes of toxicity are not related to the diet or sun exposure, but to the chronic consumption of high doses of VD supplements. This is because the body regulates the amount of vitamin D produced by sun exposure and, and even fortified foods do not have large quantities of this vitamin.

Although the recommended doses are below 2000 IU, the maximum level of daily consumption which is considered tolerable is 4000 IU for people between the ages of 1 and 18, and 10,000 IU for people over the age of 19.^[18]^ On the other hand, the doses that have been documented to lead to toxicity are above 40,000 IU to 50,000 IU per day.^[16,17]^ This is considered as potentially severe condition whose symptoms are associated to secondary hypercalcemia and are mainly of a gastrointestinal nature (anorexia, nausea, vomit, constipation, diarrhea, abdominal pain) and polydipsia, polyuria, muscular weakness and fatigue, among the most relevant.^[19]^

Therefore, the supplementation with an orally administered dose of 1000 IU/day of vitamin D is completely safe for the participants and it does not have adverse effects.

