### Data collection and statistical analysis

3.10

Taking samples, measurements, and data collection will be done by following the operating procedures manual which describes in detail each one of the procedures. Data will be digitally uploaded in real time by means of a digital questionnaire.

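### Minor: section 3.7 ties the telephone question on harms to presumed relation to the supplement; record all adverse events first and judge relation later, blind to arm

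*Protocol article*

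**What the plan says.** Section 3.7 (Follow-up) plans telephone calls to all participants at weeks 1, 2, 5, 7 and 12. It gives them two purposes. One is adherence, by self-report. The other is harms: "These calls will inquire about any “potential” adverse effects related to the intervention".

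Section 3.8 (Safety considerations) argues from dose levels. It cites tolerable daily intakes of 4000 IU (ages 1 to 18) and 10,000 IU (over 19), and documented toxicity above 40,000 to 50,000 IU per day. It concludes that 1000 IU/day "is completely safe for the participants and it does not have adverse effects". The Introduction takes a similar tone about vitamin D supplementation in general: "they are low cost, easy to implement and very safe". Section 3.6 (Interventions) is more careful and says only that the dose "is well below the intake levels associated with toxicity".

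Section 3.4 withholds the assignment from the nurse, laboratory staff, pediatrician, principal investigator and analyst, and states: "This will ensure the masking of the people in charge of measuring the outcomes, administering the intervention and analyzing the study data". Section 3.10 refers data collection to an "operating procedures manual which describes in detail each one of the procedures". That manual, the call instrument and the content of Table 1 are not shown.

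**The concern.** The usual practice for harms is to record every adverse event and to assess relation to treatment as a separate, later step. The wording in 3.7 puts relation into the question itself. A participant or caller who thinks a complaint has another cause has a reason not to mention it or write it down, and an event that is never recorded cannot be reassessed later.

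Section 3.8 adds to this. Staff who have read that the 1000 IU dose has no adverse effects have a prior reason to regard any given complaint as unrelated.

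What is at stake is the completeness of the harms data and, to a small degree, participant oversight. The Discussion says that positive results would make it possible to recommend supplementation and could inform health policy, so complete harms data would have a use.

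**Working it through.** The plan gives no harms figure to reproduce, so the check is mainly a reading of the text, with some arithmetic to show what the stated margins do and do not support.

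**1. What the 3.7 wording fixes.** The question is broad in one respect (it covers anything potential) and narrow in another (it asks for effects related to the supplement). Nothing in the article as shown says that all events are recorded whatever their cause, or that relation is judged afterwards.

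**2. Whether relation can be judged on the call.** Section 3.7 does not say who makes the calls. If it is the nurse, or any of the other staff listed in 3.4, the caller does not know the arm, and nor does the participant. Both arms also take vitamin D (1000 IU or 200 IU). Relation can therefore only be presumed during the call.

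**3. What the dose margins support.** Inputs, all from 3.8 unless noted:
- study dose 1000 IU/day (3.6)
- upper bound on recommended doses: "Although the recommended doses are below 2000 IU"
- tolerable levels 4000 and 10,000 IU
- toxic doses above 40,000 to 50,000 IU
- diet: "The recommendation of vitamin D in the diet for the Colombian population (males-females) is 600 IU/day"

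Dose alone:
- 1000/2000 = 50%
- 1000/4000 = 25%
- 1000/10,000 = 10%

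Dose plus diet, assuming the dietary recommendation is fully met (1000 + 600 = 1600 IU/day):
- 1600/4000 = 40%
- 1600/10,000 = 16%
- 40,000/1600 = 25-fold margin
- 50,000/1600 = 31.25-fold margin

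The claim that toxicity is not expected holds comfortably, even on total intake. None of these ratios is a frequency of adverse effects, so the step to no adverse effects does not follow from them.

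**4. What the trial itself could show.** With 75 participants per arm and zero events recorded in one arm, the exact upper limits on the true rate are:
- one-sided 95%: 1 − 0.05^(1/75) = 0.0392, or 3.9%
- two-sided 95%: 1 − 0.025^(1/75) = 0.0480, or 4.8%

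These limits follow from n = 75 alone and would be the same under perfect collection. They do not measure how many events the wording would lose. They show only that this trial could not establish an absence of adverse effects, and that even these limits can be read as stated only if events were not filtered when collected.

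**5. Size of the change.** 150 participants × 5 calls = up to 750 calls, all already planned.

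**The case against.** The strongest reply is that 3.7 states the purpose of the calls and does not set a recording rule. 'Any' and 'potential' both widen the question, and nothing says who judges relation or that an event thought unrelated is left out. The article is condensed. The call instrument, the operating procedures manual and the content of Table 1 are not shown, and section 3.12 commits the trial to Good Clinical Practice principles. Full event recording may well be specified elsewhere.

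Much of this stands, and it keeps the point minor. It does not change the printed phrase, which still names relation as part of what is asked and can be corrected where it stands.

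Four stronger readings are tempting, and the document does not support them:
- **That staff are told to discard events judged unrelated.** No such instruction appears. The risk comes from the wording of the question.
- **That 3.7 and 3.8 contradict each other.** Asking about effects that are not expected is ordinary monitoring, and nothing uses 3.8 to limit what is collected.
- **That complaints such as nausea or fatigue would be lost.** Section 3.8 lists these as toxicity symptoms, so the question is most likely to catch them. The events at risk are those that nobody connects with vitamin D.
- **That the harms comparison is biased.** The question, the call times and the masking are the same in both arms.

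**Conclusion.** The point holds as a minor improvement to harms data. Section 3.7 ties collection to presumed relation, which cannot be judged reliably on a masked call. Events presumed unrelated may then be missed in both arms. The number missed cannot be estimated from the document and may be small if callers read 'potential' broadly.

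Between-arm comparisons, efficacy outcomes, sample size and the primary analysis are unaffected. Adverse events are neither a primary nor a secondary outcome in section 3.9.

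The conclusion rests on two assumptions: that the callers are among the masked staff, and that the documents not shown do not already require all events to be recorded. If they do, only the article's phrase needs to be aligned with them. The overstatement in 3.8 is editorial and would not justify a finding by itself. It does not mean that the dose is unsafe, since the margins above support the expectation of no toxicity.

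**What to change.** In section 3.7, replace the harms part of the sentence with a statement that each call records all adverse events since the last contact, whatever their presumed cause, and that relation to the supplement is judged afterwards by someone blind to arm. The masking in 3.4 already makes that possible.

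As accompanying wording in 3.8, conclude that toxicity is not expected at this dose given the cited upper levels. This agrees with 3.6 and with the minimum-risk classification in 3.12.

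The cost is one phrase and one sentence, with no added contacts. The downside is more minor, unrelated events to tabulate.

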**Table 1 T1:**
[figure not shown]
Summary of measurement and follow-up activities.

### Safety considerations

3.8

The recommendation of vitamin D in the diet for the Colombian population (males-females) is 600 IU/day, a value equivalent to a nutritional density of 40 IU/1000 Kcal. In adolescence, plasma levels decrease and needs increase; however, the recommendation is the same as for adults.^[17]^

Normally there is no toxicity by VD since it is a fat-soluble vitamin and the organism excretes it regularly. Thus, the causes of toxicity are not related to the diet or sun exposure, but to the chronic consumption of high doses of VD supplements. This is because the body regulates the amount of vitamin D produced by sun exposure and, and even fortified foods do not have large quantities of this vitamin.

Although the recommended doses are below 2000 IU, the maximum level of daily consumption which is considered tolerable is 4000 IU for people between the ages of 1 and 18, and 10,000 IU for people over the age of 19.^[18]^ On the other hand, the doses that have been documented to lead to toxicity are above 40,000 IU to 50,000 IU per day.^[16,17]^ This is considered as potentially severe condition whose symptoms are associated to secondary hypercalcemia and are mainly of a gastrointestinal nature (anorexia, nausea, vomit, constipation, diarrhea, abdominal pain) and polydipsia, polyuria, muscular weakness and fatigue, among the most relevant.^[19]^

Therefore, the supplementation with an orally administered dose of 1000 IU/day of vitamin D is completely safe for the participants and it does not have adverse effects.

### Outcomes

3.9

*Primary outcome:* These are biochemical and anthropometric measurements that allow to respond to the purpose of the study. These include:

Total BMI. This requires taking the size in meters (m) and weight in kilograms (kg).Lipid profile: Measurements will be made of the serum levels of total cholesterol, low-density lipoprotein (LDL), high-density lipoprotein (HDL), and triglycerides.Serum levels of 25(OH) D.

*Secondary outcomes:* These are complementary measurements for the primary outcomes.

Waist-hip ratio: determines the intra-abdominal fat levels and is obtained by dividing the waist perimeter by the hip perimeter.Skin folds: These are taken for the indirect estimation of body fat percentage by means of measuring the bicipital, tricipital, abdominal, and subscapular folds.Fasting glycemia.

### Data collection and statistical analysis

3.10

Taking samples, measurements, and data collection will be done by following the operating procedures manual which describes in detail each one of the procedures. Data will be digitally uploaded in real time by means of a digital questionnaire.

#### Body mass index

3.10.1

The procedure will be conducted by a trained nurse. Participants must be fasting, wearing minimum clothes, without shoes, belts or other accessories that may alter the measurements. The measure of body weight will be in kilograms (kg) to one decimal place, and the size in meters (*m*) to 2 decimal places. From these measurements the BMI will be obtained using the formula: BMI = Weight (kg) / size (m)^2^.

Size will be measured with a SECA 213 stable stadiometer, that has a measuring range of 20 to 205 cm (8–81”) with features that allow an accurate reading. Weight will be measured using a SECA 813 digital scale which has a steel frame as reinforcement, fit for people weighing up to 200 kg (440 lb); the measurement is performed twice to ensure a more reliable measurement (if there is a difference of less than 0.5 kg, the second value is recorded; if it is greater than 0.5 kg, a third one should be taken and the value closest to the latter should be recorded).

#### Lipid profile

3.10.2

After a 10 to 12 hour fast, a laboratory assistant will draw a sample of peripheral venous blood through a puncture of the basilic cephalic vein or its medians and extract approximately 15 cc to 20 cc of blood. The processing and analysis of the samples will be done respectively through enzymatic technique, selective liquid detergent, selective detergent accelerator and Glycerol Phosphate Oxidase in the clinical laboratory of *Hospital Internacional de Colombia*, which is certified and has a high-quality registry.

#### 25(OH) D levels

3.10.3

25-hydroxyvitamin D are measured from the same blood samples drawn for lipid profile and quantified in serum by chemiluminescent microparticle immunoassay (CMIA).

#### Waist–hip ratio

3.10.4

Measurements will be made by the trained nurse with an inelastic tape measure in centimeters (cm) to one decimal place, directly on the skin of the abdomen and bare hip or with soft garments that do not make volume or put pressure on the tissues. The person should have both of his or her hemispheres aligned and preferably be barefoot or wear flat shoes.

The circumference of the waist shall be measured at the midpoint between the edge of the lower sack (10th rib) and the upper edge of the iliac crest, without adjusting or stopping touching the skin. With the person relaxed, 2 measurements shall be taken without removing the tape, just checking the position. If the difference between the two measurements is less than or equal to 1 cm, the average of the 2 will be taken and if the difference is greater, a third measurement will be taken and the intermediate value between the three measurements will be recorded.

For the measurement of the hip, the knees and the heels must be together; the most prominent part of the hip on both sides shall be located and the tape measure shall be passed following the same recommendations as for the circumference of the waist.

#### Skinfolds

3.10.5

These measurements will be taken by a trained nurse using a Harpender skinfold caliper. The skinfold will be taken with the index and thumb, and the caliper will be placed 1 cm inwards the fold. It will be applied for 3 seconds before taking the reading while the needle stops oscillating.

*Bicipital fold:* It shall be taken parallel to the longitudinal axis of the arm above the acromial-radial midline, on the anterior face of the arm above the mid-portion of the bicep.*Tricipital fold:* It shall be taken parallel to the longitudinal axis of the arm on the acromial-radial midline, in the posterior region of the arm on the mid-portion of the triceps.*Abdominal fold:* it shall be taken vertically, parallel to the longitudinal axis of the body, at the level of the navel, approximately five centimeters from the navel on the right side of the rectus abdominis*Subscapular fold:* the lower angle of the scapula shall be felt to determine the most prominent lower point; the fold shall be taken two centimeters from the lower angle of the scapula, in an oblique direction, downwards and outwards, forming an angle of 45 degrees with the horizontal axis.

The percentage body fat (PBF) is taken for the indirect estimation by means of measuring the bicipital, tricipital, abdominal, and subscapular folds. Percentage of body fat (%BF) calculated with the Siri equation for four skin folds (SF), like so: % BF SIRI = ((4.95/ D) − 4.5) × 100. Body density (D) is obtained using the linear regression equation proposed by Durnin and Womersley (C and D). D = C − M × log10 ∑ 4SF (bicipital, tricipital, abdominal, and subscapular).^[20]^

